### Outcomes

2.5

The outcomes defined in this protocol aim to quantify, in an integrated manner, the effects of mental fatigue on different domains of football performance, covering neurophysiological, oculometric, motor, and subjective variables. The definition of these outcomes allows for a multimodal analysis, based on objective and subjective indicators, which reflect the complexity of cognitive and motor responses under conditions of mental overload. This section describes the methodological framework and outcome measures designed to assess the multidimensional effects of mental fatigue in the neurophysiological, oculomotor, motor, and subjective domains.

#### Cortical activity (EEG)

2.5.1

Cortical electrical activity will be measured with the EMOTIV EPOC Flex EEG device, in order to assess neurophysiological changes related to mental fatigue elicited by the ST. Validation studies have demonstrated that the Emotiv system is capable of recording physiologically meaningful EEG signals and event-related potentials comparable to laboratory systems, although with lower signal-to-noise ratio and reduced reliability compared to medical-grade devices (58, 59). These findings suggest that while suitable for non-critical research applications, limitations remain when high precision or maximal signal robustness is required.

The analysis will focus on the theta (4–7 Hz), alpha (8–13 Hz) and beta (13–30 Hz) frequency bands, with an emphasis on the frontal and parietal regions, traditionally linked through processes of executive control, sustained attention, sensory-motor integration and regulation of the mental load (19, 60–62).

Although increases in frontal theta power and decreases in parietal alpha power have frequently been reported in association with sustained cognitive effort and fatigue-related states, these oscillatory changes are not specific or exclusive markers of mental fatigue. Theta and alpha modulations are influenced by multiple cognitive and attentional processes, including task engagement, vigilance, motivational state, and general mental workload (19, 60, 61). In addition, alterations in beta activity have been associated with changes in cortical stability and motor-related activation (61, 62). Therefore, in the present protocol, changes in these frequency bands will be interpreted as neurophysiological correlates associated with cognitive load and fatigue-related states, rather than definitive biomarkers of mental fatigue.

##### Selection and justification of EEG channels

2.5.1.1

Electrodes F3, F4, Fz, C3, C4, Cz, P3, P4, Pz, T3, T4, T5, T6, O1, O2, and Oz will be analysed according to the international 10–20 system, allowing comprehensive coverage of the frontal, central, parietal, temporal, and occipital regions. The frontal, central, and parietal regions are particularly sensitive to the effects of mental fatigue, showing increases in theta band power and reductions in alpha band power, phenomena associated with greater attentional effort and decreased cognitive efficiency (19, 61, 62). The temporal and occipital regions were included to ensure a comprehensive characterisation of cortical activity, as previous studies have identified changes in functional connectivity and neural complexity associated with sensory integration and visuospatial regulation under fatigue (62).

Based on explicit theoretical hypotheses, frontal midline electrodes (particularly Fz and adjacent frontal sites) are defined as primary regions of interest (ROIs), given the well-established association between frontal theta activity and mental fatigue. Posterior parietal-occipital regions are included due to their documented involvement in alpha modulation and attentional processing under cognitive load. Analyses focusing on these predefined ROIs and frequency bands (theta, alpha, beta) will be considered primary. Analyses involving additional scalp regions will be clearly identified as exploratory and interpreted with appropriate caution.

##### Spectral analysis

2.5.1.2

EEG recordings will be acquired before (Pre) and after (Post) the performance of motor tasks, allowing the evaluation of the modulation of the global cortical state between moments and experimental conditions (experimental group vs. control group) (62). The EEG recordings will be obtained under resting-state conditions before and after mental fatigue induction. As no stimulus-locked tasks are included during EEG acquisition, event-related potential (ERP) analyses are not applicable within the present design. Although full-spectrum EEG data (delta, theta, alpha, beta, and low gamma) will be acquired across all electrodes, primary analyses will focus on theta, alpha, and beta power, given their consistent association with mental fatigue in previous literature (19, 61). Connectivity-based analyses are considered beyond the scope of this protocol and may be explored in future investigations. Between group comparisons will be conducted to detect whether the ST elicits greater alterations in alpha and theta power than the control condition, thus establishing whether different cognitive demands produce distinct neurophysiological signatures of fatigue. Comparisons between moments and groups will allow the identification of cortical alteration patterns associated with fatigue-related cognitive states. However, these oscillatory modulations will be interpreted in conjunction with behavioral, oculomotor, and subjective measures, acknowledging that EEG frequency changes reflect multifactorial neural dynamics rather than isolated biomarkers of mental fatigue (19, 60, 63, 64).

Within the experimental group, pre- and post-task EEG analyses will assess the impact of the ST on cortical activation, particularly changes in frontal theta and parietal alpha bands, to capture acute neurodynamic changes resulting from cognitive overload. Recent evidence by Krukow et al. (65) supports this approach, having demonstrated that mental fatigue states are reliably associated with altered EEG connectivity and spectral profiles, especially in the theta and alpha bands, during cognitively demanding tasks. These within-group comparisons aim to detect functional adaptations linked to increased attentional effort, executive control demands, and potential declines in motor preparation efficiency.

In addition to these comparisons, correlational analyses will explore the relationships between EEG parameters and behavioral performance. Power values in the relevant bands will be examined in relation to LSPT and Y-SART results, with the aim of identifying neurophysiological predictors of motor performance under conditions of fatigue.

Furthermore, multimodal associations will be conducted to determine the degree of alignment between EEG data and other indicators of fatigue, namely the VAS and oculomotor metrics captured through the ETS. This triangulation seeks to assess the convergence between subjective, neurophysiological, and visual-attentional markers of mental fatigue.

Topographic maps (topo plots) of cortical distribution by band and experimental moment will also be generated, allowing the spatial location of power changes in the scalp to be visualized and the neurophysiological dynamics associated with mental fatigue to be characterized (15, 19, 60, 66, 67). These integrated approaches can support the identification of electrophysiological biomarkers of fatigue that reflect the brain's adaptation to cognitive effort and its consequences for motor readiness in sports contexts.

In addition, access to large EEG databases, such as the Motor Movements/Images Dataset recently organized by Shuqfa et al. (68), has driven the development of methods for classifying and analyzing real and imagined motor tasks, enabling more accurate calibrations and informing decisions about the cortical bands and locations to be monitored in experimental protocols applied to sports contexts.

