In parallel, during Phase 2, brain electrical activity will be recorded using the portable Emotiv Epoc Flex Gel Kit system, equipped with Ag/AgCl sensors arranged according to the international 10–20 system (32 channels), with reference and ground electrodes placed in standard positions. Data will be sampled at 128 Hz, ensuring impedances below 10 kΩ to guarantee signal quality. Each recording will have a total duration of five minutes, divided into three conditions: eyes open (two minutes), eyes closed (two minutes), and motor imagery (one minute). Participants will sit comfortably in a quiet environment to avoid external interference or movements that could generate artefacts. The selection of these three conditions is supported by evidence demonstrating that distinct neural states can be captured through resting conditions and motor imagery paradigms (45–47). Eyes-open and eyes-closed recordings are known to reflect different oscillatory dynamics, particularly in the alpha and theta bands (48, 49), while motor imagery reliably evokes measurable cortical activation and is sensitive to mental fatigue (50–52). In the statistical analyses, recording condition (eyes open, eyes closed, motor imagery) will be treated as a within-subject factor, allowing evaluation of whether fatigue-related changes differ across neural states.

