### Performance assessment

2.4

After collecting baseline data, participants will perform two motor tests as part of Phase 3 of the protocol. The first is the LSPT, which assesses passing accuracy and speed under time pressure in a standardized soccer-specific context. Participants perform 16 passes to designated targets announced in sequence, with performance assessed by total execution time adjusted for penalty points for technical errors (e.g., incorrect passes, errors in the target area, poor ball handling) and bonus points for accurate actions. This scoring protocol has been validated in youth and elite football players (56, 57). The test will be filmed with two cameras for subsequent technical analysis and penalty verification. A schematic representation of the LSPT setup is provided in Figure 2, adapted from Ali et al. (34).

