**Figure 3 F3:**
[figure not shown]
Schematic representation of the Y-SART, adapted from Yuan et al. (2).

After completing Phase 3, participants move on to Phase 4, where they perform the cognitive intervention defined by their group assignment, either the ST (experimental group) or a neutral task, such as reading magazines (control group). This is followed by Phase 5, which begins with participants completing the VAS again. Next, both motor tests are repeated, this time with continuous recording by the ETS. Finally, a second EEG recording is performed under the same conditions as in the initial phase, concluding the data collection session.

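### Two rounds of motor tests and the 30-minute task lie between the EEG recordings, so within-group EEG change cannot be credited to the Stroop task; only Group × Time can carry that claim

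*Protocol article*

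**What the plan says.** The order of the session can be read from sections 2.3 and 2.4 of the protocol article.

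- Baseline EEG: "during Phase 2, brain electrical activity will be recorded using the portable Emotiv Epoc Flex Gel Kit system".
- First motor tests: "After collecting baseline data, participants will perform two motor tests as part of Phase 3 of the protocol".
- Task: "After completing Phase 3, participants move on to Phase 4, where they perform the cognitive intervention defined by their group assignment". Section 2.2 sets 30 minutes for both the Stroop task and the reading task.
- Phase 5 opens with the VAS, and then both motor tests are repeated.
- Post EEG: "Finally, a second EEG recording is performed under the same conditions as in the initial phase". This ends the session.

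Section 2.5.1.2 describes the EEG contrast in two ways. One sentence places the recordings around the motor tests: "EEG recordings will be acquired before (Pre) and after (Post) the performance of motor tasks". The next says that they are "obtained under resting-state conditions before and after mental fatigue induction". For the experimental group it then says that "pre- and post-task EEG analyses will assess the impact of the ST on cortical activation".

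Section 2.6 plans paired t-tests of pre against post within each group and does not exclude EEG. It describes the EEG repeated-measures model twice. The first description has Time, Recording Condition and Group. The second names only Time and Recording Condition. Both label Time as before versus after mental fatigue.

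**The concern.** A change between two recordings reflects everything that happens between them. Here that is the cognitive task, two rounds of physical and technical testing, and the passage of time. Calling the contrast a before-and-after of mental fatigue credits all of it to one component.

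The point has practical weight. Section 2.5.1 makes beta one of the three bands of interest and itself links beta to motor-related activation. A significant pre-post change in the experimental group could be reported as an effect of the Stroop task when motor testing or time produced it. The same holds for a significant Time effect in a model without Group.

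There is a second, smaller consequence. Section 2.5.4.2 plans to correlate the post-intervention VAS with EEG power, but the post VAS is taken before the second motor tests and the post EEG after them. The two do not describe the same moment.

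**Working it through.** **1. What lies between the recordings**

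| Step | Phase | Experimental | Control |
|---|---|---|---|
| EEG 1 | 2 | yes | yes |
| LSPT and Y-SART | 3 | yes | yes |
| 30-minute task | 4 | Stroop | reading |
| VAS | 5 | yes | yes |
| LSPT and Y-SART | 5 | yes | yes |
| EEG 2 | end of 5 | yes | yes |

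Only the Phase 4 row differs by design. The within-arm change contains every row from Phase 3 on. The difference in change between arms removes what the arms share.

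**2. The plan's own figure**

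Inputs from section 2.2: two groups, two times, f = 0.25, alpha 0.05, power 80%, N = 34. The correlation between the two measurements is not stated; 0.5 is assumed.

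Noncentrality λ = f² × N × m / (1 − ρ) = 0.0625 × 34 × 2 / 0.5 = 8.5, with 1 and 32 degrees of freedom. Power is 0.807, and 34 is the smallest even N that reaches 80%, so the stated size reproduces. With ρ = 0.3 the requirement is 46, and with ρ = 0.7 it is 22.

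**3. False attribution in the within-arm test**

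Suppose that the Stroop task has no EEG effect and that motor testing plus time shift band power by δ, in units of the SD of the change score. The documents give no value for δ, so a range is shown. The paired t-test in one arm of 17 has noncentrality δ√17 on 16 degrees of freedom. The Time effect over both arms is treated as 34 change scores, with noncentrality δ√34.

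| δ (assumed) | δ√17 | Paired test, n = 17 | Time effect, N = 34 | Group × Time |
|---|---|---|---|---|
| 0 | 0 | 5% | 5% | 5% |
| 0.2 | 0.82 | 12% | 21% | 5% |
| 0.3 | 1.24 | 21% | 40% | 5% |
| 0.5 | 2.06 | 49% | 81% | 5% |
| 0.8 | 3.30 | 87% | 99.5% | 5% |

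The last column assumes that the shift is the same in both arms. More players make the within-arm problem worse. Table 1 gives 24 men and 24 women split equally between the groups, and with 24 per arm the paired test rejects in 16%, 29%, 65% and 96% for the four non-zero shifts.

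**4. What Group × Time estimates**

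In the step 2 design, f = 0.25 is a difference in change of 1 SD of change between arms (noncentrality √(17/2) = 2.92, whose square is 8.5). If part of that effect fades before the late EEG, power falls. The retained fractions are assumed.

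| Effect remaining | Power |
|---|---|
| 100% | 0.81 |
| 90% | 0.72 |
| 80% | 0.62 |
| 70% | 0.51 |
| 50% | 0.29 |

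**The case against.** The strongest defence is that the causal comparison is already in the plan. Controls go through the same sequence, section 2.6 places Group in the first description of the EEG model, and section 2.5.1.2 plans between-group comparisons. A shift common to both arms cancels there. This stands, and it confines the problem to the within-group readings. A reader might infer that the order invalidates the EEG comparison as a whole; the documents do not support that.

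A reader might also take the statement that the second EEG is made under the same conditions as a false claim of equal physical state. Section 2.3 defines three recording conditions (eyes open, eyes closed, motor imagery), and the phrase most naturally refers to those.

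The order is also disclosed, and sections 2.5.1 and 2.5.1.2 warn that EEG changes are not specific to fatigue. That is a partial answer. Neither section names the intervening motor tests or elapsed time as an explanation, and nor does section 3.1 on limitations.

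The size of the shift is unknown. The motor tests are short, no physical load is stated, and at 0.2 to 0.3 SD of change the error rate is 12% to 21%, well below the higher figures in the table. This stands as a caution on magnitude.

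Finally, testing performance first after the induction is defensible, because football performance is a central outcome. Moving an EEG recording would not make the within-arm change attributable to the Stroop task, since elapsed time and at least one round of motor tests would still lie between the recordings.

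**Conclusion.** The concern holds for three things: the experimental group's EEG change read as the effect of the Stroop task, the paired t-tests where applied to EEG, and the Time effect under its present label. None of them can separate the Stroop task from two rounds of motor tests and elapsed time.

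With no Stroop effect, the paired test in 17 players would be significant in about 12% to 87% of trials for assumed shifts of 0.2 to 0.8 SD of change, against a nominal 5%. The direction follows from the session order; the size rests entirely on the assumed shift.

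Group × Time remains valid under a common shift. It should be described as what it is: the Stroop effect still present after the motor tests, including any difference in how the arms respond to those tests. Loss of power through fading is possible, but nothing in the document measures it.

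The document does not show that the session must be reordered. That is a design choice with costs on either side.

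**What to change.** Changes to the text:

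1. In section 2.6, make Group × Time the only EEG test of the Stroop effect, and name Group in the second description of the EEG model as in the first.
2. In section 2.5.1.2, report within-arm EEG change descriptively and delete the statement that it assesses the impact of the Stroop task. State in section 2.6 that the paired t-tests are not used to infer a Stroop effect on EEG.
3. Relabel Time for EEG as pre versus post session, and reconcile the two adjoining timing sentences in section 2.5.1.2.
4. State, in section 3.1 as well, that the post EEG follows the second motor tests and is not concurrent with the post VAS, and that Group × Time therefore estimates the remaining effect.

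The cost is wording only; data collection and sample size do not change.

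Moving a recording is optional. Recording the post EEG straight after the Phase 5 VAS closes the gap with the VAS but delays the post motor tests by the five-minute recording plus cap checks. Recording the baseline EEG after the Phase 3 tests puts both recordings after motor testing but leaves the VAS gap. Neither replaces the restriction to Group × Time.

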#### Oculomotor parameters (ETS)

2.5.2

Oculomotor parameters will be monitored using the Pupil Pro Eye Tracking Headset (Pupil Labs GmbH, Germany) to assess neurophysiological changes associated with mental fatigue induced by the ST. The metrics analysed will include the number and average duration of fixations, the duration and average speed of saccades, pupil diameter, and blink rate, parameters widely recognized as sensitive indicators of cognitive load, attention regulation, and fatigue-related decline in vigilance (69–72). To minimize potential confounding influences, standardized task instructions, calibration procedures, controlled lighting conditions, and consistent testing environments will be implemented. Moreover, the within-subject pre-post design allows each participant to serve as their own control, thereby reducing the impact of inter-individual variability in visual strategies and perceptual tendencies.

In addition to descriptive characterisation, the study will include comparisons between the experimental and control groups in terms of these oculomotor parameters after the intervention phase. These comparisons will assess whether mental fatigue induced by the ST produces significant changes in visual-attentional dynamics compared to a cognitively neutral task. Specific attention will be given to variations in blink rate, pupil diameter, fixation duration, and saccade characteristics.

Within the experimental group, oculomotor parameters will be compared before and after the intervention to identify the direct impact of cognitive overload on visual attention and eye movement control. This intragroup analysis is crucial for understanding the dynamic response of the oculomotor system to cognitive stress.

In addition, correlational analyses will be performed between ETS data and behavioral performance on the LSPT and Y-SART to explore whether visual-attentional indicators predict motor performance under fatigue. A multimodal approach will also be employed to assess convergence between different markers of fatigue (ETS, EEG, and VAS), providing a comprehensive understanding of how different modalities reflect fatigue-related changes.

##### Fixations

2.5.2.1

The average duration of fixations reflects the time required for visual information processing and is directly associated with the allocation of attentional resources. Under mental fatigue, the dynamics of fixations become less efficient, typically characterized by longer fixation durations and a reduced number of fixations, reflecting slower cognitive processing and reduced efficiency in visual exploration. Empirical evidence confirms that the proportion of longer fixations (>150 ms) increases significantly under fatigue, while short fixations (<150 ms) decrease, indicating a compensatory adjustment of attention to maintain task performance despite cognitive decline (72, 73).

##### Saccades

2.5.2.2

Saccades, which represent rapid movements between fixation points, are another relevant indicator of the functional state of the oculomotor system. Given that saccadic eye movements are closely related to neural activity in the frontal lobe, it is highly likely that the use of saccades as a biomarker of mental fatigue will demonstrate high reliability and validity (63). Mental fatigue is often associated with a reduction in the speed and duration of saccades, as well as an increase in variability between successive movements, reflecting a decrease in the neural excitability of visuomotor structures and less efficient attentional control (72, 74).

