To ensure data quality and reproducibility, EEG signals will undergo standardized pre-processing procedures. Data will be processed in MATLAB R2025a (MathWorks, Natick, MA, USA) using EEGLAB v2025. Continuous recordings will be visually inspected to identify gross artifacts or recording instabilities, and non-EEG channels will be removed prior to analysis. Signals will be band-pass filtered between 1 and 45 Hz using a zero-phase finite impulse response (FIR) filter and re-referenced to a common average reference. Artifact correction will be performed using Independent Component Analysis (extended infomax algorithm). Independent components will be automatically classified using the ICLabel plugin integrated in EEGLAB, and components identified as ocular, muscular, cardiac, line-noise, or other non-brain sources with high probability (≥0.90) will be removed prior to signal reconstruction. Channels exhibiting persistent excessive noise throughout the recording will be excluded from analysis. All preprocessing procedures will be applied consistently across participants and experimental conditions to ensure methodological standardization and internal validity.

Oculomotor activity will be recorded with the Pupil Core system (Pupil Labs GmbH, Germany), with sampling at 200 Hz. This equipment will allow the analysis of fixations, saccades, pupillary dilation or and blink rate, during the LSPT. The ETS was only applied in the LSPT, as it contains visual stimuli while performing gaze orientation and control of attention, appearing as especially appropriate to analyze gaze patterns (53). In addition, the LSPT is longer in duration, which makes it possible to collect consistent eye activity data. Vansteenkiste et al. (54) demonstrated a correlation between LSPT performance and gaze patterns in young players, reinforcing that this type of test is suitable for analyzing oculomotor metrics. In contrast, the Y-SART is a simple task and it presents brief visual stimuli, so the use of an eye-tracker is not justified. Recent research has demonstrated that motor skills (e.g., sprinting, changing direction, reactive strength) are the main determinant in performance on the Y-SART and is also affected by sensory/perceptual processes to a smaller extent or indirectly (55). The data will be processed with open-source software provided by the manufacturer.

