For EEG data (theta, alpha, and beta bands), spectral power within predefined regions of interest (ROIs) will be analyzed using repeated-measures models including Time (pre vs. post mental fatigue) and Recording Condition (eyes open, eyes closed, motor imagery), allowing evaluation of fatigue-related changes across neural states. Primary analyses will focus on frontal midline and posterior ROIs, consistent with the study's theoretical hypotheses. Exploratory analyses across additional scalp regions will be conducted separately and corrected using False Discovery Rate (FDR) procedures to control for multiple comparisons. Correlational analyses (Pearson's r) will explore associations between EEG bands and behavioral performance (LSPT, Y-SART), as well as subjective fatigue scores (VAS and FAS) (94, 95). Topographic maps will be generated to visualize EEG power distributions across cortical regions.

For oculomotor parameters (fixations, saccades, pupil diameter, blink rate), comparisons will assess the impact of mental fatigue on attention dynamics and visual search efficiency. Pearson correlations will explore links between ETS metrics, EEG patterns, and motor performance scores. Eye-tracking outcomes will be interpreted in conjunction with EEG measures, motor performance variables, and subjective fatigue scores, allowing a multimodal framework that reduces interpretative ambiguity.

Motor performance will be analyzed by comparing LSPT and Y-SART results before and after cognitive induction. Metrics such as execution time, technical penalties, and reaction times will be examined to determine whether cognitive fatigue impairs decision-making and technical execution under pressure.

These performance results will be correlated with neurophysiological and oculomotor indicators to investigate predictive relationships. Subjective fatigue will be analyzed using pre and post VAS comparisons and baseline FAS scores. These will be used to triangulate subjective perceptions with objective changes in EEG, ETS, and performance data. Higher self-reported fatigue scores are expected to align with reduced cortical efficiency, altered visual behavior, and degraded motor output.

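### Saccade speed and duration, analysed without amplitude, cannot support the neural-excitability reading: a joint fall points to smaller gaze shifts, not to slower saccades of the same size

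*Protocol article*

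**What the plan says.** Section 2.5.2 (Oculomotor parameters) lists the eye-tracking metrics. Besides the number and mean duration of fixations, they are "the duration and average speed of saccades, pupil diameter, and blink rate". Section 2.3 places the recording in the LSPT: "This equipment will allow the analysis of fixations, saccades, pupillary dilation or and blink rate, during the LSPT".

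Section 2.5.2.2 (Saccades) gives the only direction stated for the saccade metrics: "Mental fatigue is often associated with a reduction in the speed and duration of saccades, as well as an increase in variability between successive movements". It then offers a mechanism, "reflecting a decrease in the neural excitability of visuomotor structures and less efficient attentional control", and rates the marker highly: "it is highly likely that the use of saccades as a biomarker of mental fatigue will demonstrate high reliability and validity".

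The safeguards against confounding in section 2.5.2 are that "standardized task instructions, calibration procedures, controlled lighting conditions, and consistent testing environments will be implemented", together with the pre-post comparison within each player. Section 2.6 (Statistical analysis) states the planned use: "For oculomotor parameters (fixations, saccades, pupil diameter, blink rate), comparisons will assess the impact of mental fatigue on attention dynamics and visual search efficiency". The same section then relates these metrics to EEG and motor scores by Pearson's r. Saccade amplitude is not mentioned in any of these sections.

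**The concern.** Duration and average speed are not free of each other: together they fix how far the eye moved. A pattern in which both fall is, for a single saccade, a pattern of smaller eye movements. A loss of excitability that slowed saccades of the same size would show as lower speed and **longer** duration.

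Saccade size can change in this task. The LSPT is a moving task of 16 passes to called targets (section 2.4), and nothing in the article holds the size of gaze shifts constant. Instructions, calibration, lighting and environment do not decide whether a player looks at the ball, the feet or the target. The within-player comparison removes stable differences between players, but not a change in looking behaviour caused by the Stroop task. The article itself expects such a change: the Introduction hypothesises poorer visual exploration, and section 2.5.3.1 describes attention drifting to irrelevant stimuli.

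What is at stake is the inference from the saccade results. Without amplitude, a result in the stated direction could be reported as reduced visuomotor excitability when gaze shifts simply became shorter. True slowing would give one metric in the stated direction and one against it. The same ambiguity passes into the correlations in section 2.6 and the multimodal integration in section 2.5.6.

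**Working it through.** The article gives no numerical saccade effect, so there is no figure to reproduce. The sample size of 34 plays no part here.

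**Inputs.** From the article: the two metrics (section 2.5.2), and the stated direction and its reading (section 2.5.2.2). Assumptions: average speed means the mean speed within a saccade, which the article does not define; all percentage changes are illustrative.

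**Step 1. Identity.** For each saccade, with amplitude A, average speed V and duration D: A = V x D.

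**Step 2. Both metrics fall by a fraction x.** New amplitude / old amplitude = (1 - x)².

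**Step 3. Speed falls by x at fixed amplitude.** New duration / old duration = 1 / (1 - x).

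| x | Amplitude change if both fall by x | Duration change if speed falls by x at fixed amplitude |
|---|---|---|
| 5% | 0.95² = 0.9025, i.e. -9.75% | 1/0.95, i.e. +5.3% |
| 10% | 0.90² = 0.81, i.e. -19% | 1/0.90, i.e. +11.1% |
| 20% | 0.80² = 0.64, i.e. -36% | 1/0.80, i.e. +25% |

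**Step 4. Smaller saccades with no slowing.** Assume duration scales as A^b with 0 < b < 1, so speed scales as A^(1 - b). For a 20% smaller amplitude:

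| b | Duration, 0.8^b | Speed, 0.8^(1 - b) |
|---|---|---|
| 0.1 | -2.2% | -18.2% |
| 0.5 | -10.6% | -10.6% |
| 0.9 | -18.2% | -2.2% |

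Both metrics fall for every exponent tried, which is the direction given in section 2.5.2.2.

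**Step 5. Worked example (assumed values).** A saccade of 8 degrees at 200 deg/s lasts 8/200 = 40 ms.
- Slowing of 10% at 8 degrees: 180 deg/s and 8/180 = 44.4 ms.
- Shrinkage to 6.48 degrees: 180 deg/s and 6.48/180 = 36 ms.

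Speed is the same in both cases. Duration moves in opposite directions, and it is the shrinkage that gives the joint fall.

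**Step 6. From single saccades to means.** The metrics will be summaries, and mean(A) = mean(V) x mean(D) + cov(V, D). Write c for cov(V, D) / [mean(V) x mean(D)]. Then mean(A) = mean(V) x mean(D) x (1 + c). If c is stable, the results above carry over. For mean amplitude to stay unchanged while both means fall by 10%, (1 + c) would have to rise by a factor of 1/0.81 = 1.235. In a simulation with varying amplitudes and b = 0.5, the means behaved like single saccades: -10.6% for both metrics when amplitude alone fell by 20%, and -10% speed with +11.1% duration when slowing alone was applied.

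**The case against.** The strongest reply is that the article claims less than a reader might infer.

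- **Prediction.** A reader might take section 2.5.2.2 as a formal prediction that the identity refutes. It is worded as an association from the literature. The hypothesis in the Introduction is only about visual exploration in general, and section 2.6 sets no directional saccade test. Nor does the identity make the association false: both metrics do fall when saccades shrink. This stands. It remains true that no other direction is given for these metrics.
- **Confounding.** A reader might infer that both saccade outcomes are invalid. The documents do not support that. Sections 2.5.2 and 2.6 aim largely at attention and visual search, and section 2.5.2.2 names attentional control as well. For that aim, shorter gaze shifts after the Stroop task may be part of the effect. This stands, and it confines the problem to the oculomotor or neural-excitability reading.
- **Consequences.** A reader might infer that individual players would be classed as showing oculomotor fatigue, or that the composite marker rests on these metrics. The article contains no classification rule and no formula or saccade weight for a composite. Section 2.6 says that eye-tracking results will be read together with the other measures. This stands too, although joint reading does not hold amplitude constant.
- **Detail.** The metric list is not expressly closed, and saccade processing is often left to a fuller document. In part this is fair. But the article itself fixes the two metrics and attaches a mechanism to their joint fall, and that pairing is what fails.
- **Means.** The identity is exact for single saccades only. Step 6 shows the condition needed for means.

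**Conclusion.** The point holds in a limited form. Saccade duration and average speed, taken without amplitude in a task that does not fix saccade size, cannot separate a change in gaze strategy from oculomotor slowing. A joint fall indicates smaller gaze shifts: 19% smaller if each metric falls by 10%. Slowing at equal amplitude would lengthen duration, by 11.1% for a 10% loss of speed. The excitability reading attached to the joint fall is therefore unsupported by the planned metrics.

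The between-group comparison of each metric remains a valid estimate of the effect on that metric. Smaller saccades may still bear on the attentional aim. Sample size and error rate are untouched.

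The conclusion assumes that average speed is the mean within a saccade and, for recording-level means, that the speed-duration covariance is stable relative to the product of the means. How much amplitude would actually change in the LSPT is unknown, so the percentages show direction and scale and are not forecasts. This is an interpretability defect in one set of outcomes. It is worth correcting because the data needed are already to be collected.

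**What to change.** In sections 2.5.2 and 2.5.2.2, with a matching line in section 2.6:

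1. Derive the amplitude of each saccade from the gaze record, and define average speed as the mean within the saccade.
2. Report amplitude beside speed and duration, as a gaze-strategy outcome.
3. Add an analysis of saccade speed conditional on amplitude, for example a per-saccade model of log speed on log amplitude with participant, time and group, including the group-by-time term. Make this the basis for any conclusion about oculomotor slowing or neural excitability.
4. State that the cited joint reduction in speed and duration is not the pattern expected from slowing at equal amplitude, where duration would lengthen.

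Keep the unadjusted comparisons. Amplitude is measured after the intervention and may be changed by it, so the conditional analysis is not protected by randomisation in the same way. It should supplement the unadjusted comparison and not replace it.

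The cost is some wording and slightly more processing, with no new procedure. The Abstract says that no data are yet available, so the change can be prespecified.
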